## Abstract

**Background:**

*Chlamydia trachomatis* is the most commonly diagnosed bacterial sexually transmitted infection in the developed world and diagnosis rates have increased dramatically over the last decade. Repeat infections of chlamydia are very common and may represent re-infection from an untreated partner or treatment failure. The aim of this cohort study is to estimate the proportion of women infected with chlamydia who experience treatment failure after treatment with 1 gram azithromycin.

**Methods/design:**

This cohort study will follow women diagnosed with chlamydia for up to 56 days post treatment. Women will provide weekly genital specimens for further assay. The primary outcome is the proportion of women who are classified as having treatment failure 28, 42 or 56 days after recruitment. Comprehensive sexual behavior data collection and the detection of Y chromosome DNA and high discriminatory chlamydial genotyping will be used to differentiate between chlamydia re-infection and treatment failure. Azithromycin levels in high-vaginal specimens will be measured using a validated liquid chromatography – tandem mass spectrometry method to assess whether poor azithromycin absorption could be a cause of treatment failure. Chlamydia culture and minimal inhibitory concentrations will be performed to further characterize the chlamydia infections.

**Discussion:**

Distinguishing between treatment failure and re-infection is important in order to refine treatment recommendations and focus infection control mechanisms. If a large proportion of repeat chlamydia infections are due to antibiotic treatment failure, then international recommendations on chlamydia treatment may need to be re-evaluated. If most are re-infections, then strategies to expedite partner treatment are necessary.

## Background

Over 100 million men and women worldwide are infected with chlamydia at any point in time [1]. It is the most commonly reported bacterial sexually transmitted infection (STI) in developed countries, with over 1.4 million cases reported in the United States in 2011 [2]. Left untreated, chlamydia can ascend from the endocervix to the upper genital tract in women and cause pelvic inflammatory disease (PID) which can increase the risk of developing fallopian tube scarring, potentially leading to ectopic pregnancy, tubal infertility and chronic pelvic pain [3-5]. In addition, genital infection in pregnant women increases the risk of preterm delivery, can be passed on to the baby during vaginal delivery and may result in eye and lung infections in the new born [3,6]. Infection with genital chlamydia can also increase the risk of HIV acquisition in both men and women, and cause epididymo-orchitis in men [4,7].

Repeat chlamydia infections are common following treatment. Among women who tested positive in an Australian cohort of 1116 young women who were treated at recruitment, 18% tested positive again at 3 months (95% CI: 8%, 34%) [8]. In the UK, a prospective cohort of 16 to 24 year old women treated for chlamydia in general practice, reported a repeat infection rate of 29.9% per year (95% CI: 19.7%, 45.4%) [9]. Another cohort of adolescent women in the US reported a repeat infection rate of 34% per year [10] and a recent systematic review of chlamydia repeat infection following treatment found that the overall median proportion testing positive again for chlamydia was 13.9% [11].

Repeat infections are generally considered to be re-infections through exposure to an infected partner. However, emerging evidence suggests that treatment failure following azithromycin may account for a substantial proportion and this has led to considerable debate in the medical and scientific literature [12-16]. Among female participants in a partner treatment trial who reported no sexual intercourse after treatment, 22 of 289 (8%; 95% CI: 5%, 11%) had persistent infection suggestive of treatment failure at follow up [17]. Similarly, the treatment failure rate in a cohort of adolescent females was 7.9% (95% CI: 4%, 10.1%) [10]. Both of these studies attempted to differentiate between re-infection and treatment failure using sexual behavior questionnaires. Batteiger et al. (2010) included genotyping as a further tool to identify re-infections, but these studies were based on self-report of sexual behavior which may have been unreliable.

The recommended first line treatment for uncomplicated genital chlamydia infection in most developed countries is a 1 gram dose of the macrolide antibiotic, azithromycin [18-20]. Although doxycycline 100 mg twice daily for 7 days is a second line treatment for uncomplicated chlamydia, it is not widely used because there are concerns about compliance given the longer duration of treatment [21]. A meta-analysis of chlamydia treatment reported a 97% cure rate for azithromycin and 98% for doxycycline [22]. Of the 12 trials included in the meta-analysis, 11 used culture or immunoassay rather than the more sensitive nucleic acid amplification tests (NAAT) to determine microbial cure at study end [22]. Given the use of culture rather than NAATs, it is possible that the treatment efficacies in these trials were over-estimated [12,13,23].

Governments throughout the developed world are pushing for increased chlamydia testing and the Australian government has invested in a large chlamydia screening randomized controlled trial [24]. It is imperative, therefore, to rigorously investigate the adequacy of currently recommended treatment for chlamydia. We describe here a cohort study, the Australian Chlamydia Treatment Study (ACTS), that aims to measure the proportion of chlamydia infected women who fail treatment when treated with 1 gram azithromycin using advanced microbiological techniques to differentiate between re-infection and treatment failure.

### Research aim

The primary aim is to estimate the proportion of women infected with chlamydia who fail treatment with 1 gram azithromycin, the most widely recommended first line treatment for genital chlamydia infection [18-20]. The secondary aim is to determine the role of *C. trachomatis* organism load, azithromycin tissue absorption of azithromycin and antimicrobial resistance in chlamydia treatment failure.

## Methods/design

### Study design and setting

This is a cohort study of women who test positive for genital chlamydia at one of two large, publically funded sexual health centres in Melbourne and Sydney, Australia. Participants will be followed up for up to 56 days post treatment and will provide weekly genital specimens for further assay.

### Duration of study

Recruitment commenced in October of 2012 and is expected to continue until October 2014, with results reported late 2015.

### Participant eligibility

Women who are diagnosed with genital chlamydia and who meet eligibility criteria will be invited to participate in the study. The study is limited to women because of their increased risk of serious chlamydia related complications.

The inclusion criteria are:

• Female;

• Positive test for genital chlamydia using Nucleic Acid Amplification Test polymerase chain reaction [PCR] (performed on specimens collected from women recruited from Sydney Sexual Health Centre) or strand-displacement assay (performed on specimens collection from women recruited from Melbourne Sexual Health Centre);

• Age ≥16 years;

• Adequate English and comprehension skills to give informed consent;

• Able to attend their recruitment clinic for follow up and specimen collection at day 7;

• Resides in a jurisdiction serviced by one of the two clinics and plan to stay in the jurisdiction for the next 8 weeks.

The exclusion criteria are:

• Current infection detected as a part of a routine test for re-infection [18];

• Concomitant infection with another bacterial STI;

• Concurrent PID;

• Self report of antibiotic use in the last 2 weeks;

• Current commercial sex work;

• Women who do not wish to receive study packs by post;

• Women who do not have a mobile phone;

• HIV positive status;

• Concurrent medication likely to significantly interact with azithromycin (e.g. cyclosporine, digoxin);

• Known macrolide allergy.

### Recruitment

Women who have tested positive for chlamydia will be seen by a research nurse at a participating clinic at point of treatment. The research nurse will explain the study to them, assess eligibility and take informed consent. The research nurse will collect specimens for further testing (Table 1) and provide treatment with a single dose of 1 gram azithromycin. The nurse will observe the participant as she takes her treatment to ensure compliance. This is classified as the baseline visit (Day 0). All clinic visits, pathology costs and treatment for participants and their partners will be provided free of charge.

**Table 1 T1:** Specimen collection by study timeline.

**Specimen collection and testing**										**If PCR positive @ d28, 42 or 56**
Day	0^d^	7	14	21	28	35	42	49	56	
Number of swabs collected	4	2	2	2	2	2	2	2	2	4-5
Culture	X									X
PCR^a^	X	X	X	X		X		X		X
Chlamydia organism load^a^	X	X	X	X	X	X	X	X	X	X
Genotype^a^	X	X	X	X	X	X	X	X	X	X
Sequencing^a^	X	X	X	X	X	X	X	X	X	X
Y-chromosome^a^		X	X	X	X	X	X	X	X	X
β-globin^a^	X	X	X	X	X	X	X	X	X	X
Test of cure^b^					X		X		X	
Az absorption^a^		X								
Blood	X									X
Rectal swab^c^										X
Location	Clinic^e^	Clinic^e^	Home^f^	Home^f^	Home^f^	Home^f^	Home^f^	Home^f^	Home^f^	Clinic^e^

^a^Processed in batches throughout the course of the study.

^b^Chlamydia PCR done in real time to report results back to participants and treat any women diagnosed chlamydia positive.

^c^If anal sex reported.

^d^Day 0 = baseline or at time of recruitment.

^e^Swabs collected by research nurse and put immediately into the appropriate medium.

^f^Self-collected high-vaginal swabs.

Key: X = specimen processed for this experiment, PCR polymerase chain reaction, Az *absorption* azithromycin absorption, d day.

### Primary outcome

The primary outcome is the proportion of women who are classified as having chlamydia treatment failure following detection of chlamydia on a self-collected high-vaginal specimen using a polymerase chain reaction (PCR – see below) Specimens will be collected for testing on days 28, 42 or 56 after recruitment (referred to as ‘test of cure’ specimens for the purpose of this study) according to the algorithm in Figure 1. This algorithm follows a previously described method [10] with the addition of the detection of Y chromosome DNA and performing high discriminatory chlamydial genotyping. Y chromosome DNA will be used to validate sexual behaviour data because it can be detected in the vagina for up to 14 days after unprotected intercourse with a male partner [25,26]. Specimens will be collected from participants every 7 days for Y chromosome detection and genotyping will be undertaken on any chlamydia positive specimens collected on days 28, 42 or 56 after recruitment. Chlamydial genotype fingerprinting will be performed to determine any differences in chlamydia strain/serovar between a participant’s baseline specimen and any repeat positive specimens detected at day 28, 42 or 56 [27]. If a woman has the same serovar present at follow up, further testing by multilocus sequence typing (MLST) targeting *ompA* and five house-keeping genes will be undertaken [28,29]. Detection of same MLST type without detection of Y chromosome DNA or any reports of unprotected sex will be classified as treatment failure. If the woman has a different serovar, it will be classified as a re-infection. A repeat positive chlamydia diagnosis will also be classified as a re-infection if the woman’s repeat specimen has the same MLST type and Y chromosome is detected or she reports unprotected sexual contact.

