### Genotyping & quantification of organism load

Chlamydial fingerprinting will be conducted on specimens that are PCR positive at baseline and at test of cure. We will determine the organism load, identify the chlamydia serovar(s) (genovar) of each infection through a series of quantitative PCR assays to establish whether or not the genotype of the chlamydia detected in those women who have a repeat positive is the same as the type present at baseline [27]. Initial qPCR primers and probes have been designed to predict antigenic differences in major outer membrane protein (MOMP) to determine the serovar as previously described [27,36-38]. The primary chlamydia group-specific multiplex quantitative PCR will target conserved regions of the *ompA* gene specific to all chlamydia serovar groups, including the B group (serovars B, E, D, L1, and L2), C group (serovars A, C, H, I, J, K, and L3) or intermediate group (serovars F and G) serovars. This assay will enable quantification of organism load and will be used to direct serovar-specific PCRs to determine serovars present in the specimen, including possibility of mixed serovars [27,39].

Chlamydia organism load in each specimen will be quantified by comparing the crossing-threshold of each specimen to the crossing-threshold of a standard curve constructed by amplifying different known copy numbers of the *ompA* gene. The beta globin gene, present at one haploid copy per nucleated cells [40], will also be quantified using qPCR to assess specimen adequacy as well as to measure sampling variability between participants and specimens by correlation with the number of eukaryotic cells collected. The quantity of chlamydia will be divided by the number of eukaryotic cells and expressed as the number of organisms present per 100 eukaryotic cells [40].

Specimens from participants where the same serovar has been detected at baseline and follow up will undergo further discriminatory confirmation of relatedness using sequencing of *ompA* gene, as well as five house-keeping genes (*hctB,* CT058, CT144, CT172, and CT682 [*pbpB*]) utilizing a multilocus sequence typing (MLST) approach [28,29,41,42]. This will include the amplification and sequencing [29,43,44] followed by determining MLST type using *C. trachomatis* MLST database (mlstdb.bmc.uu.se).

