### Data collection

Participants will be asked to complete questionnaires at the time of recruitment and each week until they reach study endpoint. The following data will be collected:

• Age, height, weight

• Genital symptoms

• Reason for attending clinic for their initial test

• Current medications including contraceptives and concurrent antibiotics

• Date of last menses

• Sexual practice data including number of sexual partners, type of sexual partners (casual, occasional, once off or regular), type of sexual contact (vaginal or anal sex), condom use; and

• Whether partners have been notified and treated

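### The written failure/re-infection rule has no term for a same-type infection already detected before first exposure, and its typing limit conflicts with Table 1

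*Protocol article*

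**What the plan says.** All references are to the protocol article.

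- **Typing.** The Primary outcome section states that "genotyping will be undertaken on any chlamydia positive specimens collected on days 28, 42 or 56 after recruitment", and that strain differences are sought "between a participant’s baseline specimen and any repeat positive specimens detected at day 28, 42 or 56". The section Genotyping & quantification of organism load sets the same limit: "Chlamydial fingerprinting will be conducted on specimens that are PCR positive at baseline and at test of cure".
- **Failure rule (Primary outcome).** "Detection of same MLST type without detection of Y chromosome DNA or any reports of unprotected sex will be classified as treatment failure".
- **Re-infection rule (Primary outcome).** A different serovar is re-infection. So is a positive where the "repeat specimen has the same MLST type and Y chromosome is detected or she reports unprotected sexual contact".
- **Weekly schedule (Table 1, under Recruitment).** PCR is marked on days 7, 14, 21, 35 and 49 as well as day 0. Load and genotype are marked in every column: "Chlamydia organism load^a^ X X X X X X X X X X" and "Genotype^a^ X X X X X X X X X X". The table key defines an X as a specimen processed for that test, and a footnote says these tests are run in batches.
- **Stated use of serial chlamydia results.** The Statistical analysis section names a linear regression of organism load over time. No visible text uses the intermediate results for classification.

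**The concern.** The primary aim is the proportion of women who fail treatment, and the Discussion presents the separation of failure from re-infection as a strength. For a woman with the same MLST type at baseline and at test of cure, the written rule turns entirely on whether there is any evidence of exposure. It does not ask whether chlamydia of that type was already detected after treatment and before the exposure.

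In this group the error runs one way: true failures with any exposure are moved to re-infection and the failure proportion falls. Exposure is unlikely to be rare, because women are advised to avoid sex for only 7 days (Partner notification) while follow-up runs to day 56. The study contrasts about 8% with the 2-3% of older culture-based work, so a downward shift of a few percentage points bears directly on its conclusion.

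There is also a plain inconsistency. Two sections limit genotyping to baseline and test-of-cure positives, while Table 1 marks it at every time point.

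**Working it through.** **1. The plan's own figure.** Inputs from Sample size estimates: p = 0.08, half-width d = 0.025. n = 1.96² × 0.08 × 0.92 / 0.025² = 452.4, close to the stated 450. The Wald interval for 36/450 is 5.49% to 10.51%, matching the stated 5.5% to 10.5%. The sample size reproduces and is not affected by this point.

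**2. The rule applied to one woman.** She is PCR positive with her baseline type on day 21, has her first unprotected act after day 21, and is positive with the same MLST type on day 28. Her day-21 specimen is outside the typing limit. The exposure triggers the re-infection rule, which has no condition on timing. She is called re-infected.

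**3. Who a timing rule could reclassify.** Suppose only specimens from day 21 on count, taken before the first evidence of exposure, with no negative in between.
- Positive at day 28: only the day-21 specimen qualifies, so first exposure must fall between days 21 and 28.
- First positive at day 42 or 56, all specimens returned: a negative test of cure lies two weeks earlier, so only the day-35 or day-49 specimen qualifies. First exposure must again fall in the last week.

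**4. Illustration.** From the protocol: n = 450 and 8%. Assumed, because the documents do not give them: half of true failures exposed; all positives at day 28; first exposures uniform over days 7 to 28; 50% to 80% of eligible women already positive with the same type.
- True failures: 0.08 × 450 = 36.
- Exposed and called re-infected: 0.5 × 36 = 18. Reported: 18/450 = 4.0%, Wald 95% CI 2.2% to 5.8%.
- Eligible under step 3: (28 − 21)/(28 − 7) = 1/3, so 6 of 18.
- Reclassified: 6 × 0.5 = 3 to 6 × 0.8 = 4.8.
- Second estimate: (18 + 3)/450 = 4.7% to (18 + 4.8)/450 = 5.1%.

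**5. Range over the exposed share e.** Primary rule: 8% × (1 − e). Second rule: 8% × (1 − e + e × s), with s = 1/3 × 0.5 = 0.167 to 1/3 × 0.8 = 0.267.

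| e | Primary rule | Second rule |
|---|---|---|
| 20% | 6.4% | 6.7%-6.8% |
| 40% | 4.8% | 5.3%-5.7% |
| 50% | 4.0% | 4.7%-5.1% |
| 60% | 3.2% | 4.0%-4.5% |
| 80% | 1.6% | 2.7%-3.3% |

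In this illustration the primary-rule estimate is below the planned lower limit of 5.5% at e = 40% and above. At e = 50% its interval excludes 8% and includes 3%.

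**The case against.** **A strict definition may be intended.** The algorithm is said to follow a published method with Y-chromosome detection and genotyping added. Calling every exposed same-type positive a re-infection protects the specificity of failure. This stands, and it is a good reason to keep the rule as primary. It does not make the resulting proportion an unbiased estimate, and the text does not describe it as conservative.

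**Early positives may be residual DNA.** A reader might infer that a same-type positive before exposure proves that the infection pre-dates it. The documents do not support that. A woman with residual DNA on day 21 who is re-infected by the same untreated partner on day 22 shows the same pattern. The protocol places its first test of cure at day 28, and nothing in it validates day 21 as a cut-off. This stands, and it is why a timing rule belongs beside the primary rule and not in its place.

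**Larger gains.** It is tempting to assume that 50% to 80% of all 18 exposed failures could be recovered, giving (18 + 9)/450 = 6.0% to (18 + 14)/450 = 7.1%. That ignores step 3: exposures between days 7 and 21 cannot be resolved by specimens from day 21 on.

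**Other stronger readings.** It would be wrong to say that all weekly data are ignored, since the Y-chromosome swabs and questionnaires are used. Nor is partner treatment ("Whether partners have been notified and treated") shown to be unused in analysis: it is absent from the classification, but the list of risk factors in Statistical analysis is open-ended.

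**Figures 1 and 2 are not shown.** A branch using serial results cannot be excluded. However, the Primary outcome text states the rule in words without exception, and the laboratory section repeats the typing limit.

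**Conclusion.** The point holds for the chlamydia results. As written, classification uses only the baseline and test-of-cure chlamydia findings, and any exposed woman with a same-MLST repeat positive is called re-infected whatever her earlier specimens showed. The primary proportion is closer to a lower bound on treatment failure. It is not a strict bound, because a re-infection with no detected exposure would be counted as failure. The conflict between Table 1 and the two typing passages is real in any case.

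The size cannot be derived from the documents. Under the assumptions in the illustration the estimate moves from 4.0% to about 4.7%-5.1%. That is a modest gain, and about 13 to 15 of the 18 misclassified failures stay on the re-infection side. The two proportions therefore show sensitivity to the rule. They should not be read as limits that enclose the true risk. The documents do not support the conclusion that the primary rule is invalid or must be replaced.

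**What to change.** 1. Reconcile the Primary outcome and Genotyping sections with Table 1, so that for women with a positive test of cure the PCR-positive weekly specimens that can inform the rule (day 21 on) are typed.
2. Keep the present rule as primary and describe it as conservative for treatment failure.
3. Pre-specify a second classification. A same-MLST positive counts as treatment failure if a specimen from day 21 on, taken before the first Y-chromosome detection or reported unprotected sex, was already PCR positive with the same type, with no negative in between.
4. Report both proportions with 95% CIs.

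**Cost.** A few extra typings of stored specimens, usually one per woman with a positive test of cure when all specimens are returned. Table 1 already schedules this work, and batch processing does not prevent retrospective classification. The downside is that some early positives may be residual DNA, so the second rule may count some re-infections as failures. That should be stated beside the estimate.

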**Figure 1 F1:**
[figure not shown]
Algorithm for classifying treatment failure.

### Study endpoint

A study participant will reach the study endpoint when she is diagnosed with treatment failure, re-infection or treatment success. The study endpoint will be measured by a test of cure PCR conducted after 28, 42 or 56 days follow up according to Figure 2.

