### Data analysis

#### Sample size estimates

To detect a treatment failure risk of 8% with a 95% CI of 5.5%, 10.5%, 450 women are required. If the risk of treatment failure is observed to be 3% (as reported by the earlier meta-analysis [22]), then a sample size of 450 generates a 95% CI of (1.7%, 5.0%). To account for a loss to follow up of 15% based on previous studies [8], 520 women will be recruited.

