### Statistical analysis

The population risk of treatment failure will be estimated as the observed proportion of women in the sample with treatment failure, with 95% CI calculated assuming an underlying binomial distribution. Multinomial logistic regression will be used to explore the association between the three-level outcome variable (treatment failure, treatment success, re-infection) and risk factors such as the impact of organism load, azithromycin absorption and MIC. One advantage of a multinominal model over two separate logistic regression models (one comparing the prevalence of treatment failure with treatment success, the other comparing the prevalence of re-infection with treatment success) is that the question of whether treatment failure and re-infection share common risk factors can be addressed formally by comparing estimated odds ratios generated by the same model. Linear regression analyses will investigate trends in chlamydia organism load over time and explore any associations with symptoms, chlamydia serovar and participant age. Both linear and multinomial regression models will be implemented with fixed and random regression effects to accommodate the longitudinal and repeated measures nature of the data. All analyses will be conducted in Stata 12.0.

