### Loss to follow up

The provision of reimbursement payments throughout the study is paramount to maximize retention. Women will be reimbursed with vouchers totalling up to $100 to cover their transport and time costs during the study. This will be broken down into smaller payments, $25 at their first follow up visit, $10 for their day 14 specimen, $10 for their day 21 specimen, $25 for their day 28 specimen and then $30 upon completion of the study (day 56 specimen or earlier if repeat positive). Reimbursements will reflect how many specimens and questionnaires are returned.

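### The planned binomial proportion cannot use women lost after a negative day-28 or day-42 test; how they are counted moves a true 8% by up to about 1.3 points, in a direction the visible text does not fix

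*Protocol article*

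**What the plan says.** All references are to the protocol article.

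- Study endpoint: "A study participant will reach the study endpoint when she is diagnosed with treatment failure, re-infection or treatment success". It continues: "The study endpoint will be measured by a test of cure PCR conducted after 28, 42 or 56 days follow up according to Figure 2". The picture itself is not available here.
- Loss to follow up, on the last voucher payment: "then $30 upon completion of the study (day 56 specimen or earlier if repeat positive". The only early completion described is a repeat positive.
- Data collection: "Participants will be asked to complete questionnaires at the time of recruitment and each week until they reach study endpoint".
- Primary outcome: positive specimens from any of days 28, 42 and 56 enter the algorithm that separates treatment failure from re-infection, so a woman negative at day 28 can still become a failure.
- Statistical analysis: "The population risk of treatment failure will be estimated as the observed proportion of women in the sample with treatment failure", with a 95% CI from a binomial distribution.
- Sample size estimates: 450 women give 8% with a CI of 5.5% to 10.5%. Recruitment is raised to 520: "To account for a loss to follow up of 15% based on previous studies".

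**The concern.** Follow-up length depends on the result. A woman positive at day 28 already has a complete outcome and cannot be lost afterwards. A woman negative at day 28 still has swabs to post from days 35, 42, 49 and 56 before her outcome is complete, and can be lost at any of them. Such loss is plausible: $70 of the $100 in vouchers ($25 + $10 + $10 + $25) is paid by day 28, and the remaining $30 comes only at completion.

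A simple proportion must either leave out a woman lost after a negative test or call her a success. Leaving her out over-represents the day-28 positives, who are always retained. Calling her a success misses any failure that would have shown at day 42 or 56. Neither error shrinks with more enrolment. The study sets out to tell a failure risk near 8% from one of 2-3%, so a shift of a point or more in the primary estimate matters.

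**Working it through.** **The plan's own figures.** With a half-width of 2.5 points, n = 1.96² × 0.08 × 0.92 / 0.025² = 452.4, against 450 stated. For 15% loss, 450 / 0.85 gives 530 and 450 × 1.15 gives 518, against 520 stated. For 3% at n = 450 the Wilson interval is 1.8% to 5.0% and the exact interval 1.6% to 5.0%, against 1.7% to 5.0% stated. The sample size reproduces and is not in dispute.

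**Inputs.** The true failure risk F is 8% or 3% (Sample size estimates). Two quantities are not in the document and are assumed over a range:
- the share e of failures first detected at day 28, from 0 to 100%;
- the loss d among women negative at day 28, from 5% to 15%. The value 15% puts the full planned loss rate there.

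For simplicity, loss falls between day 28 and day 42 and is unrelated to later outcome.

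**Formulas.** Let F28 = eF, FL = (1 − e)F, and A = all positives at day 28. With no re-infection, A = F28.

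- Dropouts excluded: [F28 + (1 − d)FL] / [A + (1 − d)(1 − A)]
- Dropouts counted as successes: F28 + (1 − d)FL

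Example with F = 8%, e = 50%, d = 15%:
- excluded: (0.04 + 0.85 × 0.04) / (0.04 + 0.85 × 0.96) = 0.074 / 0.856 = 8.6%;
- counted as successes: 0.074 = 7.4%.

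With e = 100%, exclusion gives 0.08 / (0.08 + 0.85 × 0.92) = 0.08 / 0.862 = 9.3%.

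| True risk | Loss d | Failures found at day 28 | Excluded | Counted as successes |
|---|---|---|---|---|
| 8% | 15% | 100% | 9.3% | 8.0% |
| 8% | 15% | 75% | 9.0% | 7.7% |
| 8% | 15% | 50% | 8.6% | 7.4% |
| 8% | 15% | 25% | 8.3% | 7.1% |
| 8% | 15% | 0% | 8.0% | 6.8% |
| 8% | 5% | 100% | 8.4% | 8.0% |
| 8% | 5% | 0% | 8.0% | 7.6% |
| 3% | 15% | 100% | 3.5% | 3.0% |
| 3% | 15% | 0% | 3.0% | 2.55% |

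Each rule is unbiased only at one extreme of failure timing; between the extremes both are biased, in opposite directions. At a true 8% the two rules differ by 1.2 to 1.3 points at 15% loss, whatever the timing, and by about 0.4 points at 5% loss. An assumed 6% re-infection changes the excluded column by 0.1 point or less: with all positives at day 28, 0.08 / (0.14 + 0.85 × 0.86) = 9.2%.

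**If late failures drop out more often.** Keep 15% loss among day-28 negatives overall, with half the failures late, and let late failures drop out at 30%. The others then drop out at (0.15 × 0.96 − 0.30 × 0.04) / 0.92 = 14.35%. Exclusion gives (0.04 + 0.70 × 0.04) / 0.856 = 7.9%. With late failures lost at 45%, it gives 0.062 / 0.856 = 7.2%. The upward bias has reversed.

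**Cumulative incidence in the same example.** The day-28 risk is 0.04. Among retained day-28 negatives the later risk is 0.034 / 0.816 = 0.0417. The total is 0.04 + 0.96 × 0.0417 = 0.08, so the true value is recovered.

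**The case against.** A reader might infer more: that women lost after a negative day 28 come only from the success side, so the plan overstates failure. The document does not support this. The Primary outcome section allows a first failure at day 42 or 56, so later failures are lost too. With loss unrelated to later outcome, exclusion biases upward only if failures are a larger share of the day-28 positives than later failures are of the day-28 negatives.

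It also cannot be said that the plan uses completers. The Statistical analysis section does not define its denominator, and the 15% allowance does not say whether a woman with a negative day 28 and nothing later counts as lost. That negative women continue to day 56 is drawn mainly from the voucher schedule. Figure 2 may hold the endpoint rule, and its absence here is not a fault of the plan. The 9.3% is a corner case, and even it lies inside the planned 5.5% to 10.5% interval.

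Finally, missing-data rules are commonly left to the full protocol or analysis plan. That would dispose of a complaint about a missing rule. It does not dispose of this point, because the article itself names the primary estimator, and that estimator has no means of using partial follow-up under either counting rule. Figure 2 could settle which rule applies, and so which of the two biases is incurred, but not make a simple proportion use the partial data.

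**Conclusion.** The concern holds in conditional form. Follow-up ends early for positives and runs to day 56 for negatives, first failures can be late, and the stated binomial proportion does not accommodate loss in between. At a true 8% and 15% loss among day-28 negatives, the estimate is expected to read 8.0% to 9.3% if dropouts are excluded and 6.8% to 8.0% if they count as successes. The largest shift, 1.3 points, is about half the planned 2.5-point half-width. At 5% loss the shift is at most 0.4 points either way, and a true 3% reads at most 3.5%.

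These figures rest on assumed failure timing, an assumed loss after day 28, and loss unrelated to later outcome. Without the last assumption, exclusion can also understate failure. No direction of bias can be attributed to the plan as published.

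**What to change.** In Statistical analysis, define the primary risk as the day-56 cumulative incidence of treatment failure over the three test-of-cure times (Aalen-Johansen estimator). Treat re-infection as the competing event, censor each woman at her last returned negative test of cure, and give a 95% CI. Report the binomial proportion under both denominators, dropouts excluded and dropouts counted as successes, as sensitivity analyses, so that the reader sees how far the counting rule moves the result.

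This changes analysis wording only: no extra specimens or visits, and the test dates and results are already collected. The cost is a slightly more complex primary analysis than a single proportion. It still assumes that dropout is unrelated to later outcome, so it does not remove bias from late failures dropping out more often.
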